### Other outcome parameters

Recurrence rate is assessed as second major outcome parameter (hypothesis 2). To keep proper medical records on recurrent patella dislocations, the patients are interviewed by telephone on a monthly basis (in addition to the abovementioned visits at the hospital).

The apprehension test is assessed by an experienced observer during the abovementioned routine clinical visits (grade 0, no evasion; grade 1, slight evasion/avoidance; grade 2, gross evasion/avoidance; grade 3, patient too anxious to allow the test).

Joint degeneration is assessed preoperatively and every three years postoperatively by means of MRI (PD-FSE with fat-sat high-resolution in all three planes/T1-TSE, sagittal/T2 weighted, isotrope 3D sequence sagittal reformatted in all three planes). The semi-quantitative MRI Osteoarthritis Knee Score (MOAKS scoring) is applied to rate the degenerative changes determined by MRI [56]. The MOAKS scoring is determined by always the same experienced musculoskeletal radiologist. Additionally, TT-TG distance is measured on postoperative MRI.

In addition, the Patella Instability Severity Score is assessed for exploratory reasons [57].

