### Hypotheses

It is hypothesized that patients with primary LPD when treated either conservatively or surgically (tailored stabilizing procedure) will show significant differences *after two years* in terms of the Banff Patellofemoral Instability-Instrument (BPII) 2.0 (hypothesis 1). We assume as well that the abovementioned groups also differ significantly in terms of recurrent patella dislocations (hypothesis 2).

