### Dropouts and exclusion of the clinical trial

To account for 20% attrition during the study period (“dropouts”), it is planned to recruit 80 patients per study group (160 overall) at baseline (see section “Statistics”). If patients request *after* randomization on their own free will a different treatment method — for example, if a patient requests surgery in conservative group — they have to be excluded from the study.

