## Outcome parameters

### Patient-reported outcome

The Banff Patellofemoral Instability-Instrument (BPII) 2.0 was reported as valid, reliable, and responsive patient-reported outcome tool in the field of patellofemoral instability [48, 49] and is used in the validated German version [50]. The BPII 2.0 serves as one of two major outcome instruments (hypothesis 1).

For exploratory reasons, the following further patient-reported parameters will be assessed in both groups: As second disease specific score, patients accomplish the Kujala Score [51] which was quoted as a reliable, valid, and responsive tool for patellofemoral disorders [52, 53]. In addition, the Short-Form 12 is used (version 2, German; SF-12v2) [54] to determine the general health outcome and the Marx activity scale to rate a patient’s physical activity [55]. The Marx Score asks for the highest activity in the last year. For postoperative monitoring of a patient’s activity, a “modified version of the Marx Score” will be used that refers to the last 2 months.

All abovementioned outcome scores are self-administered and will be assessed preoperatively, 6 and 12 months postoperatively, and then yearly. Those scores are collected during routine visits at the hospital. Alternatively, the questionnaires for assessment of the outcome scores can be filled out online by the patients to reduce dropouts.

The follow-up period is planned for 2 years. However, with the patient’s consent, the period can also be prolonged.

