### Statistics

Patient characteristics will be presented as means, standard deviations, and percentages. The main analysis will use linear mixed models that allow data modeling with a varying number of assessments per patient and time-varying covariates. Such a model will be used to compare the differences in changes over time between the two study groups. The following terms will be included in the model: a random baseline, a first-order autocorrelation covariance matrix, a fixed-effect patient group, a fixed effect time point, and the group-by-time interaction (reflecting the intervention effect). The BPII 2.0 will serve as the primary outcome parameters. The main analysis is “intention to treat” and will focus on the group difference in the change of BPII 2.0 scores between pre-op and 2-year follow-up. The abovementioned secondary outcome parameters will be analyzed with the same model.

Power/sample size analysis was done for the comparison of the two study arms at a 2-year follow-up with regard to the BPII Score. As there are no specific minimal important difference (MID) for the BPII available from the literature, we defined the MID to be 0.5 standard deviations following general recommendations from the literature [58]. A sample size of N = 64 per study arm (128 overall) provides 80% power (alpha = 0.05, two-tailed) to detect a difference of 0.5 standard deviations in a t-test for independent samples. To account for 20% attrition during the study period (“dropouts”), we plan to recruit 80 patients per study group (160 overall) at baseline.

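### Hypothesis 2 counts only re-dislocations, so stabilising surgery on a conservatively treated knee before it re-dislocates is not captured as a failure, and the comparison can favour the conservative arm

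*Protocol article*

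**What the plan says.** Under Hypotheses, the protocol article assumes that the "groups also differ significantly in terms of recurrent patella dislocations (hypothesis 2"). Under Other outcome parameters it gives this endpoint its rank: "Recurrence rate is assessed as second major outcome parameter (hypothesis 2"). The same section gives the purpose of the monthly contact: "To keep proper medical records on recurrent patella dislocations, the patients are interviewed by telephone on a monthly basis", in addition to the hospital visits. Neither part of the Outcome parameters section names later stabilising surgery on the index knee as an outcome.

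Two other places bear on what happens to a conservatively treated patient who is later operated on. Dropouts and exclusion of the clinical trial covers patients who ask for the other treatment after randomisation: "if a patient requests surgery in conservative group — they have to be excluded from the study". The Statistics section says: "The main analysis is “intention to treat” and will focus on the group difference in the change of BPII 2.0 scores". Neither place says how an operated knee is scored for recurrence, and the article has no rule for an operation that the patient did not request.

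Under Surgical group, every patient allocated to surgery receives MPFL reconstruction. On follow-up, the article says: "The follow-up period is planned for 2 years".

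**The concern.** The arms are not symmetrical on this point. Surgical patients have their stabilisation as the allocated treatment, so a first stabilising operation outside the allocated treatment can arise only in the conservative arm. The surgical arm can have only revisions. An operation done because a knee remains unstable is reasonably regarded as a failure of conservative treatment. It also lowers the chance that the knee later has the one event being counted.

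The second major outcome may therefore lose events mainly in one arm. The difference tested in hypothesis 2 would shrink, and a conservative arm kept stable partly by later surgery could look closer to primary surgery than the conservative strategy deserves. If the operations are not recorded as they happen, with date and reason, the information may not be recoverable at analysis.

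**Working it through.** **The plan's own figure.** The sample size is set for the BPII 2.0: a difference of 0.5 SD, two-sided alpha 0.05, 64 per arm. The t-test power at 64 per arm is 0.801, and 64 / (1 - 0.20) = 80 per arm recruited. Both reproduce. The article gives no rate and no power for hypothesis 2, so nothing can be reproduced for that endpoint.

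**Inputs for the illustration.** From the article: 64 analysed per arm, two-sided alpha 0.05. Assumed, because the article gives no values:
- 2-year re-dislocation without crossover: conservative pC = 0.30, surgical pS = 0.10
- share of the conservative arm operated on before re-dislocating: s = 0.10
- share of those knees that would otherwise have re-dislocated: q = 0.40 to 0.60
- no re-dislocation after the later operation

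**Formulas.**
- Kept as non-events: observed rate = pC - s·q
- Excluded: observed rate = (pC - s·q) / (1 - s), with 64 × 0.9 = 57.6 patients left in the conservative arm
- Power = Φ((d - 1.96·SE0) / SE1), where d is the difference in rates, SE0 uses the pooled rate and SE1 the separate rates

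**Without crossover.** The pooled rate is 0.20. SE0 = √(0.16 × 2/64) = 0.0707. SE1 = √((0.21 + 0.09)/64) = 0.0685. Power = Φ((0.20 - 0.1386)/0.0685) = 0.82.

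**With crossover.**

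| Handling of operated knees | q | Observed conservative rate | Power against 10% |
|---|---|---|---|
| Kept as non-events | 0.40 | 0.30 - 0.04 = 26.0% | 0.66 |
| Kept as non-events | 0.60 | 0.30 - 0.06 = 24.0% | 0.56 |
| Excluded | 0.40 | 0.26/0.90 = 28.9% | 0.76 |
| Excluded | 0.60 | 0.24/0.90 = 26.7% | 0.67 |
| Excluded | 0.30 (average risk) | 0.27/0.90 = 30.0% | 0.80 |

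In the last row there is no bias; the power is lower only because patients are lost.

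**Relaxing the assumptions.** If operated knees still re-dislocate at the surgical rate, the kept figures rise by 0.10 × 0.10 = 1 point, to 25-27%. For conservative risk 20-40%, 5-20% operated, and operated knees at average or double risk, keeping them as non-events lowers the conservative rate by 1 to 16 points; excluding them lowers it by 0 to 10 points.

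**Counting surgery as failure.** The conservative rate becomes 0.24 + 0.10 = 34% to 0.26 + 0.10 = 36%. With an assumed 2% revision rate in the surgical arm (12% failure), power is 0.85-0.90. With 5% (15% failure), it is 0.71-0.78, below the 0.82 without crossover.

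**The case against.** The strongest objection is that nothing in the article says an operated knee counts as recurrence-free. A reader might infer that every conservatively treated knee stabilised before re-dislocation is scored as a success. The text does not support this. The one rule given removes patients who request surgery from the study, so they leave both numerator and denominator. Intention to treat is stated for the BPII 2.0 analysis, and on surgery the patient did not request the article is silent. This part of the objection stands: for patients who request surgery, bias depends on their carrying above-average risk, and it is smaller than under the non-event reading.

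Two further over-readings should be avoided. The monthly call is described by its purpose of recording dislocations, which does not show that it records nothing else; the Documentation section also has important harms recorded in each group. And surgery in the conservative group is given as a conditional example, not as an expectation.

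It can also be said that re-dislocation is a concrete event, used as an outcome in all seven studies in Table 1, and that instability without dislocation is measured elsewhere, by the BPII 2.0 and by the apprehension test: "The apprehension test is assessed by an experienced observer during the abovementioned routine clinical visits". That is a good reason to retain the endpoint. It does not repair hypothesis 2, because those measures lie outside it and later surgery may improve them by 2 years.

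Finally, the handling of a later operation is often left to an analysis plan, which is not shown here. That is fair for the analysis detail. An analysis plan cannot, however, restore data on patients no longer followed or on operations not recorded at the time.

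**Conclusion.** The point holds in a limited form. As written, hypothesis 2 does not capture stabilising surgery before re-dislocation as a failure of the conservative strategy. Exclusion favours the conservative arm only if the excluded knees carry above-average risk, which is plausible when instability prompts the request but is not shown. Keeping the patient as a non-event favours that arm whenever more of those knees would have re-dislocated than do so after the operation. Applying intention to treat to hypothesis 2 would therefore not settle the matter by itself: it moves patients who request surgery from the first situation to the second.

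The size cannot be derived from the article. On the assumed rates, the 20-point difference falls to 14-16 points if operated patients are kept and to 16.7-18.9 points if they are excluded. These figures illustrate the mechanism and do not forecast the trial's result. The change is worth making because it is cheap and the information may be lost if it is not collected prospectively.

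**What to change.** 1. Keep re-dislocation as the stated endpoint of hypothesis 2.
2. Keep following all randomised patients for hypothesis 2, including those who switch treatment, and reconcile Dropouts and exclusion of the clinical trial with the intention-to-treat statement under Statistics.
3. Prespecify one supporting analysis by randomised group, counted from randomisation. Failure is the first of re-dislocation of the index knee or stabilising or revision surgery on it for instability after the allocated treatment, whoever initiated the operation. Report both components by arm, beside the re-dislocation result.
4. Add one question to the existing monthly call: any operation on the index knee since the last call, with date, procedure and reason.

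The cost is protocol wording, one question in a call already made, and continued contact with patients who switch. No visits or additional recruitment are needed. The drawback is that the decision to operate is unblinded and discretionary, and some operated knees would never have re-dislocated. The combined failure result should therefore support the re-dislocation result and not replace it. No power gain should be claimed for it, since its power depends on an unknown revision rate in the surgical arm.

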### Statistics

Patient characteristics will be presented as means, standard deviations, and percentages. The main analysis will use linear mixed models that allow data modeling with a varying number of assessments per patient and time-varying covariates. Such a model will be used to compare the differences in changes over time between the two study groups. The following terms will be included in the model: a random baseline, a first-order autocorrelation covariance matrix, a fixed-effect patient group, a fixed effect time point, and the group-by-time interaction (reflecting the intervention effect). The BPII 2.0 will serve as the primary outcome parameters. The main analysis is “intention to treat” and will focus on the group difference in the change of BPII 2.0 scores between pre-op and 2-year follow-up. The abovementioned secondary outcome parameters will be analyzed with the same model.

Power/sample size analysis was done for the comparison of the two study arms at a 2-year follow-up with regard to the BPII Score. As there are no specific minimal important difference (MID) for the BPII available from the literature, we defined the MID to be 0.5 standard deviations following general recommendations from the literature [58]. A sample size of N = 64 per study arm (128 overall) provides 80% power (alpha = 0.05, two-tailed) to detect a difference of 0.5 standard deviations in a t-test for independent samples. To account for 20% attrition during the study period (“dropouts”), we plan to recruit 80 patients per study group (160 overall) at baseline.

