## Methods

### Study design and participants

A prospective, randomized-controlled trial design is applied. Before commencement of the study, approval of the ethical committees (EC) of the participating centers is obtained. Patients with objective, unilateral first time LPD, based on patient’s history and physical examination, will be considered for participation. After written informed consent the patients are included in the study at their first visit at the emergency department. Excluded are (a) patients with osteochondral lesions requiring removal/refixation, (b) patients with recurrent LPD, (c) pregnant patients, and (d) patients > 45 years of age and patients with physical maturity Kramer stage 1 to stage 3a [44, 45].

Clinical workup includes thorough history, physical evaluation, plain radiographs, and magnetic resonance imaging (MRI) in all patients. When the physical examination reveals suspicion of maltorsion syndrome, MRI (or CT scan) is done of the hip, knee, and ankle to quantify femoral and tibial torsion. When the physical examination reveals suspicion of a relevant genu valgum or varum a long-standing x-ray is performed.

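### The fixed random-baseline plus first-order autocorrelation covariance may misstate the standard error of the primary BPII 2.0 change contrast by up to roughly 10% in either direction

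*Protocol article*

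**What the plan says.** The Statistics section lists the terms of the main model: "a random baseline, a first-order autocorrelation covariance matrix, a fixed-effect patient group, a fixed effect time point", together with "the group-by-time interaction (reflecting the intervention effect"). The main analysis "will focus on the group difference in the change of BPII 2.0 scores between pre-op and 2-year follow-up".

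Under Patient-reported outcome, the scores "will be assessed preoperatively, 6 and 12 months postoperatively, and then yearly", and "The follow-up period is planned for 2 years". The visits that bear on the primary contrast are therefore at 0, 6, 12 and 24 months, with gaps of 6, 6 and 12 months. Under Study design and participants, "the patients are included in the study at their first visit at the emergency department", so the baseline score belongs to the period just after the injury.

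The article does not say whether the autocorrelation structure has equal or visit-specific variances, or whether its lag counts visits or months. It gives no BPII 2.0 SD by visit and no within-patient correlation.

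**The concern.** Taken in its usual form, the named structure has only three parameters: a between-patient variance, a residual variance and one autocorrelation. It makes the spread of scores at injury equal to the spread at 24 months. It also makes the correlation of baseline with 6 months equal to that of 6 with 12 months and of 12 with 24 months.

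A baseline taken shortly after a dislocation is the visit least likely to fit that pattern, and the primary contrast uses it directly. If the structure does not fit, the model-based variance of the change differs from the true one. The p-value and confidence interval of the primary test are then not at their nominal level. Four fixed visits and at least 128 patients do not call for so tight a restriction.

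**Working it through.** **The plan's own figure.** "A sample size of N = 64 per study arm (128 overall) provides 80% power (alpha = 0.05, two-tailed") for a difference of 0.5 SD in a t-test. With 126 degrees of freedom and noncentrality 0.5 × √(64/2) = 2.83, power is 0.801; at 63 per arm it is 0.795. Allowing for 20% attrition, 64/0.80 = 80 per arm. The figures reproduce. They do not use the mixed model, so nothing below changes them.

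**Set-up.** Index the visits at 0, 6, 12 and 24 months as 1 to 4.
- Model covariance in its usual form: V(j,k) = σb² + σ²ρ^|j−k|.
- Primary contrast within a patient: c = (−1, 0, 0, 1).
- Model variance of the change: c'Vc = 2σ²(1 − ρ³).
- True variance of the change: c'Sc = s0² + s24² − 2·r·s0·s24, where r is the baseline to 24-month correlation.

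With group, time and their interaction all in the model and complete data, the estimate is the simple difference in mean change whatever V is. Only the standard error is at risk. The patient number cancels in R = model SE / true SE = √(c'Vc / c'Sc), and actual alpha = 2[1 − Φ(1.96R)]. For each assumed S, the parameters of V are those that minimise log|V| + tr(V⁻¹S), which is where the likelihood fit settles in large samples.

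**Examples.** All SDs and correlations are assumptions. SDs are in units of the follow-up SD.

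| Assumed truth | σb², σ², ρ fitted | c'Vc | c'Sc | R | alpha |
|---|---|---|---|---|---|
| A. Correlation 0.2 + 0.8 × 0.7^(months/6), equal SDs | 0.179, 0.820, 0.639 | 1.212 | 1.216 | 0.999 | 0.050 |
| B. As A, baseline SD 0.7 | 0.123, 0.716, 0.608 | 1.110 | 0.941 | 1.086 | 0.033 |
| C. As A, baseline SD 1.2 | 0.184, 0.961, 0.664 | 1.360 | 1.499 | 0.952 | 0.062 |
| D. Baseline correlates 0.1 with each follow-up, 0.7 among follow-ups, equal SDs | 0.135, 0.862, 0.417 | 1.599 | 1.800 | 0.942 | 0.065 |
| E. As D, baseline SD 0.7 | 0.119, 0.734, 0.435 | 1.347 | 1.350 | 0.999 | 0.050 |
| F. Baseline correlates 0 with follow-ups, 0.8 among follow-ups, baseline SD 1.2 | 0.000, 1.127, 0.512 | 1.951 | 2.440 | 0.894 | 0.080 |

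Row B in full: r = 0.2 + 0.8 × 0.7⁴ = 0.392; c'Sc = 0.49 + 1 − 2 × 0.392 × 0.7 = 0.941; c'Vc = 2 × 0.716 × (1 − 0.608³) = 1.110; R = √(1.110/0.941) = 1.086; alpha = 2[1 − Φ(2.129)] = 0.033.

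**Range.**
- Spacing alone (equal SDs, correlation decaying with calendar time, as in row A): R 0.993 to 0.999 with complete data and 0.983 to 0.990 with 20% dropout completely at random. Alpha is 0.050 to 0.054 over both.
- Unequal SDs (baseline 0.6 to 1.2 times the later SD), a weakly correlated baseline, or both: over 40 assumed matrices, R 0.90 to 1.09 with complete data (alpha 0.033 to 0.078) and 0.91 to 1.07 with the same dropout (alpha 0.036 to 0.074). A second set of 40 gave 0.88 to 1.08 with complete data (alpha 0.034 to 0.084).
- Unstructured covariance: R = 1.00 and alpha = 0.05 in every case, in large samples.

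**The case against.** A random intercept with first-order autocorrelation is a recognised repeated-measures model. The article wants a model that copes with a varying number of assessments and allows follow-up to be prolonged, and a sparse structure suits that. Heterogeneous-variance and continuous-time versions of the structure exist and the text excludes neither. An analysis plan that is not shown may settle the form, the degrees of freedom and a fallback. All of this stands. It limits the point to the structure as named, read in its usual form.

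A reader might go further in four ways that the document does not support.
- That the primary standard error is wrong. It depends on SDs and correlations that the article does not give, and in rows A and E it is right.
- That the 6, 6 and 12 month gaps are the problem. The random intercept and the fitted autocorrelation absorb almost all of the uneven spacing.
- That larger errors, which can arise for a cross-sectional 2-year difference or a baseline-adjusted comparison from such a model, apply here. Hypothesis 1 and the power calculation refer to 2 years, but the Statistics section names the change from baseline as the main analysis, and no baseline-adjusted model is planned.
- That the treatment estimate is biased. With complete data it is unchanged. Dropout that depends on earlier scores could shift it under a poorly fitting covariance, but the article gives nothing from which to size that, so it is not counted here.

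**Conclusion.** The point holds as a modest, conditional weakness. If the acute baseline differs from later visits in variance, or correlates weakly with them, the standard error of the primary contrast may be misstated by up to roughly 10%. The error can go either way. A baseline with a larger SD or a weak correlation tends to make the test too liberal, a smaller baseline SD pushes it towards conservative, and the two can cancel. Actual two-sided alpha runs from about 0.03 to 0.08 instead of 0.05. The liberal end needs a near-zero baseline correlation or a larger baseline SD, and the document establishes neither.

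The figures assume the homogeneous, visit-indexed form, large samples and, where dropout is included, dropout completely at random. This is a cheap improvement and not an error that invalidates the analysis.

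**What to change.** For the primary analysis, use the 0, 6, 12 and 24 month data only, and leave any prolonged follow-up to a separate analysis. Replace the random baseline and first-order autocorrelation with an unstructured 4x4 covariance and no added random intercept. Fit by REML with Kenward-Roger or Satterthwaite degrees of freedom, and name the single 24-month group-by-time contrast as the test. If the model does not converge, use a heterogeneous-variance structure with robust standard errors.

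The cost is about one line of wording. The covariance has 4 × 5/2 = 10 parameters instead of 3, so seven more, which is small with 128 to 160 patients. The planned numbers of 64 and 80 per arm do not change.

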In synopsis of the abovementioned studies, there is no consensus on whether patients with first time LPD should be treated conservatively or surgically (Table 1). Besides, in most of those studies the surgically group was uniform, meaning that all patients were treated with the same surgical procedure. In addition, previous studies have focused more on the rate of re-dislocation and were not based upon modern and relevant PROM scores. Treatment with the same surgical procedure is regarded as a major limitation as surgical treatment of LPD should be done in a tailored manner, depending on the patient’s anatomic pathologies which lead to LPD [10, 11]:

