### Surgical group

The surgical treatment is performed in a tailored manner, addressing the respecting pathologic anatomy that predisposes to LPD. MPFL reconstruction is performed in every patient. Other surgical techniques listed below will be applied in individual combinations, dependent on patient’s needs.

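### The main model uses none of the prognostic baseline data collected in every patient, so a valid comparison gives up precision that prespecified adjustment could recover

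*Protocol article*

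**What the plan says.** The Statistics section does not leave the main model open. It names a random baseline, a first-order autoregressive covariance and "a fixed-effect patient group, a fixed effect time point, and the group-by-time interaction (reflecting the intervention effect". The section notes that this class of model can take covariates that vary over time, but it names none.

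Baseline anatomy is nevertheless collected in both arms. Under Study design and participants: "Clinical workup includes thorough history, physical evaluation, plain radiographs, and magnetic resonance imaging (MRI) in all patients". Torsion imaging and the long-standing x-ray are additional and are done only when the examination raises suspicion.

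Anatomy also decides what the surgical arm receives. The Introduction holds that "surgical treatment of LPD should be done in a tailored manner, depending on the patient’s anatomic pathologies which lead to LPD". The Surgical group section gives every patient MPFL reconstruction and adds: "Other surgical techniques listed below will be applied in individual combinations, dependent on patient’s needs". The MPFL reconstruction part of the Introduction links many failures to isolated reconstruction in knees with severe bony pathology.

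The sample size is set for the overall comparison of arms: "we defined the MID to be 0.5 standard deviations following general recommendations from the literature", and 64 per arm is said to suffice "to detect a difference of 0.5 standard deviations in a t-test for independent samples".

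**The concern.** The protocol itself ties anatomy to dislocation and to failure of surgery, and age and sex are known for everyone. These are natural candidates for prognostic variables for BPII 2.0 and for recurrence. A model that omits them leaves whatever variance they explain in the residual, so the confidence interval for the treatment effect is wider than it need be.

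The trial has 80% power under its own assumptions, with no margin beyond the dropout allowance. Some precision could be had without recruiting anyone, if the covariates are fixed before the data are seen. They also have to enter the model in a form that affects the estimate of interest, and the obvious form does not.

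**Working it through.** **Inputs from the Statistics section.** Two-sided alpha 0.05, 64 evaluable per arm, difference 0.5 SD, 20% dropout, 80 recruited per arm.

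**Assumed, because the documents give no figure.** The share R² of the variance of the analysed contrast explained by the covariates is taken as 5 to 20%. The share p of patients with an anatomical feature is taken as 50% or 30%.

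**1. The plan's own figure.** The two-sample t-test needs 63.77, so 64 per arm; power at 64 is 80.1%. Recruitment is 64 / 0.8 = 80. Both figures reproduce.

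**2. Possible gain from adjustment.** The standard error in SD units is sqrt(2/64 × (1 − R²)), and the effective standardised difference is 0.5 / sqrt(1 − R²).

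| R² | Standard error (SD) | Effective difference | Power, 64 per arm |
|---|---|---|---|
| 0 | 0.177 | 0.500 | 80.1% |
| 5% | 0.172 | 0.513 | 82.1% |
| 10% | 0.168 | 0.527 | 84.1% |
| 20% | 0.158 | 0.559 | 88.1% |

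The standard error falls by 1 − sqrt(0.95) = 2.5% to 1 − sqrt(0.80) = 10.6%. This is equivalent to having 64 / 0.95 = 67 to 64 / 0.80 = 80 evaluable patients per arm.

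**3. Main effects alone do not deliver this gain.** The target is the difference between arms in change from baseline to two years. Let m be the observed mean, S and C the arms, 0 and 24 the months, x̄ the arm mean of a covariate and b its slope, the same at every visit. With complete data the adjusted contrast is

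[(m_S24 − b·x̄_S) − (m_S0 − b·x̄_S)] − [(m_C24 − b·x̄_C) − (m_C0 − b·x̄_C)] = (m_S24 − m_S0) − (m_C24 − m_C0).

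The covariate cancels and the estimate is exactly the unadjusted one. If the slope may differ by visit, the adjusted contrast differs from the unadjusted one by −(b_24 − b_0)(x̄_S − x̄_C). Only then does the covariate act on the contrast and take variance out of it. The powers in step 2 are therefore those of a t-test on a contrast whose residual variance has been reduced. They carry over to the planned model only if covariate-by-time terms are included and R² refers to that contrast.

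**4. How much an arm-by-anatomy estimate could show.** For a two-level feature with share p in each arm, the standard error of the interaction is sqrt(2/(64p) + 2/(64(1 − p))).

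- p = 50%: sqrt(2/32 + 2/32) = 0.354 SD. The 95% interval is ±1.96 × 0.354 = ±0.69 SD. The interaction detectable with 80% power is 2.80 × 0.354 = 0.99 SD, and power for a 0.5 SD interaction is 29%.
- p = 30%: sqrt(2/19.2 + 2/44.8) = 0.386 SD. The detectable interaction is 1.08 SD, and power for 0.5 SD is 25%.

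Even with an even split, the half-width of the interval exceeds the 0.5 SD that the plan treats as the minimal important difference.

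**The case against.** The strongest reply is that nothing is wrong with the model. The aim and both hypotheses ask for an overall difference between two strategies in first-time dislocators, and the group-by-time term estimates that. This stands.

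A reader might infer more from the emphasis on anatomy, and three such inferences fail.

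- One is that the protocol's premise is that the benefit of surgery over conservative care varies with anatomy, so that a single average effect misses the point. The text says that the operation should match the anatomy. It states no hypothesis that the effect against conservative care differs by anatomy.
- Another is that an anatomical interaction would test tailoring. That would need a comparison with uniform surgery, and no arm receives it.
- A third is that chance imbalance in anatomy biases the result. Under randomisation, such imbalance is part of the sampling error that the standard error already reflects.

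It can also be said that covariates and subgroups usually belong in an SAP, which is not shown. For subgroups and interactions this is right, and their absence is no finding. It is weaker for the main model, whose terms the article lists.

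Two practical objections also stand. The 5 to 20% has no source in the documents, and working with change from baseline may already remove variance that the covariates share with the baseline score. In addition, torsion and femorotibial angle are not imaged in everyone, and coding them as absent where no image exists risks misclassification.

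**Conclusion.** The point holds as a modest improvement in precision, not as the repair of an invalid analysis. The listed model is valid for the stated aim but uses no baseline prognostic variable, although several are available for all patients.

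If age, sex and MRI-based anatomy explain 5 to 20% of the variance of the analysed contrast, power at 0.5 SD with 64 per arm goes from 80% to about 82 to 88%. If they explain less, the gain is smaller; if they explain nothing, there is none. The figures assume that the covariates enter with time-specific slopes.

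The documents do not support reading the omission as a failure to test the trial's premise. Any estimate by anatomy would be exploratory and imprecise: about ±0.69 SD at best under the stated assumptions.

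**What to change.** In the Statistics section, or in the SAP before any outcome data are seen:

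- Prespecify three baseline covariates: age, sex and a count of anatomical features assessable in every patient. The count uses the protocol's own criteria: TT-TG distance at or above 18 mm, Caton-Deschamps Index above 1.2, and high-grade trochlea dysplasia.
- Have the features read from the baseline MRI without knowledge of arm. The article does not say whether the MRI is complete before randomisation, so blinded reading is the safeguard and the enrolment workflow need not change.
- Leave femoral torsion and femorotibial angle out of the count, because they are imaged only on suspicion.
- Enter each covariate in the BPII model with its covariate-by-time terms, and as a covariate in the recurrence analysis. Keep the listed unadjusted model as a sensitivity analysis.
- Optionally, report one arm-by-anatomy estimate with its confidence interval, labelled exploratory, and state that it does not test tailoring.

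The cost is wording, blinded reading of images already taken, and a few degrees of freedom. With four assessments up to two years and one parameter per covariate, the BPII model gains 3 × 4 = 12 coefficients, three for each visit. Sample size and treatment do not change.
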